## Abstract

**Introduction::**

Cardiac rehabilitation (CR) is strongly indicated in patients with acute myocardial infarction (MI), and has been proven to reduce mortality and recurrence and improve patients quality of life. Although clinical guidelines for CR have already been developed domestically and internationally, hospital-based CR remains underutilized. Currently, studies exploring strategies to improve CR participation in South Korea and Asia are limited.

**Objectives::**

This study aims to compare the effect of providing CR financial incentives to post-MI patients referred for outpatient CR and to confirm the effect of increasing CR participation and completion rates.

**Methods::**

This single-blind, pragmatic, randomized controlled trial will be conducted at 2 tertiary hospitals for CR after acute MI. The control and experimental groups will be randomized, with each group consisting of 24 participants (total of 48 participants) assigned in a 1:1 ratio. The experimental group will receive 4, 7, and 11 USD per completed session of CR during the 1st to 12th, 13 to 24th, and 25th to 36th sessions of CR, respectively, for 3 months after enrollment. Participants who completed the 36 sessions will receive 260 USD incentives. The primary outcomes at 3 months will be used to assess the CR participation rate, as the number of CR sessions completed, and CR completion, as attendance of sessions greater than 50%, thus completion of ≥18 sessions. The outcomes will be used to compare changes in cardiorespiratory function (VO_2_ max, VO_2_ at anabolic threshold), the Korean activity scale index, EuroQol 5 dimensions, and the patient health questionnaire at 3 months after discharge and 6 and 12 months after baseline.

**Discussion::**

Providing financial incentives may confirm the effect of increasing CR on participation and completion rates.

## 1. Introduction

Cardiac rehabilitation (CR), which consists of supervised exercise programs, patient education, risk factor management, and stress control, is a customized intervention for patients with cardiovascular disease. CR has been most strongly indicated in patients with acute myocardial infarction (MI),^[1]^ and various studies have demonstrated its effect in reducing mortality, recurrence, and hospital readmissions while improving exercise capacity and quality of life.^[2–4]^

Although strong recommendations and benefits of CR have been emphasized in the literature, the actual participation rate in CR remains low worldwide. Among CR-eligible Medicare beneficiaries in the United States, only 24.4% participated in CR, of whom 26.9% completed the CR program.^[5]^ In Japan, CR participation rates were estimated to be as low as 3.8% to 7.6%.^[6]^ Globally, approximately 38.8% to 54.7% of countries have provided CR,^[6,7]^ but CR participation remains at approximately 30% to 40% worldwide.^[6,8]^

According to a global CR density report published in 2019, the CR density in South Korea was 22, ranking 27th out of 111 countries with CR programs.^[9]^ A national study reported CR density as approximately 10 AMI incidences/capacity/year, indicating that 10-fold more CR institutions are required for the yearly AMI incidence, with only 1.5% of acute myocardial infarction patients (960/64,982) participating in outpatient CR after discharge. Thus, despite CR coverage by the National Health Insurance, hospital-based CR remains underutilized in South Korea.^[10]^ Moreover, despite enrollment in outpatient CR starting at 47%, adherence to the program has decreased to 17% in regional cardiocerebrovascular centers in South Korea.^[11]^ Surveys of the medical staff in these centers indicated that time, distance, and transportation issues were relevant barriers to CR, followed by cost burdens. Additionally, a larger study questioning CR attenders compared with non-attenders indicated that patients identified logistical factors, such as distance, cost, and transportation problems, as major barriers to center-based CR.^[12]^ A systematic review analyzing studies of CR participation in the USA and Europe reported that lack of transportation or distance from CR facilities were important factors for low CR adherence.^[13]^

Various intervention strategies have been implemented worldwide to increase participation and adherence to CR. A previous study by Gaalema et al^[14]^ reported a significant increase in CR participation with doubling of CR completion in patients with low socioeconomic status in the US by providing financial incentives to CR-eligible patients. Currently, there are insufficient studies exploring strategies to improve CR participation in South Korea and in Asia, in general.

We hypothesized that issues of transportation difficulties, cost burden, and time could be alleviated by providing financial incentives. Therefore, this study examines the efficacy of financial incentives as transportation aids for increasing CR participation and completion among acute MI patients in South Korea.

## 2. Methods

### 2.1. Study design and protocol registration

This study is a single-blind, pragmatic, randomized control trial with an allocation ratio of 1:1, implemented until June 2023. This randomized control trial was registered at the Clinical Research Information Service (CRIS, WHO International Clinical Trials Registry Platform as the 11th member of the Primary Registry: Registration No: KCT0006063). This protocol was developed based on the guidelines of the Standard Protocol Items: Recommendations for Interventional Trials (SPIRIT, https://www.spirit-statement.org/).

### 2.2. Study setting

Patients at 2 tertiary hospitals, Chungnam National University Hospital and Chonnam National University Hospital, will be screened for inclusion.

### 2.3. Subjects and recruitment

Among the patients who visited the hospital for outpatient CR, the study objectives will be explained and patients who provided consent will be selected and recruited. Separate recruitment notices will be posted in the therapy rooms of the rehabilitation center and outpatient clinics of the Department of Rehabilitation Medicine and Department of Cardiology. Banners for recruitment will be installed at the entrance of the hospital’s main building.

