#### 2.3.1. Selection criteria.

-Male and female patients aged between 19 and 85 years.-Patients hospitalized for acute MI and referred for outpatient CR after acute treatment and discharge.-Patients who agreed to participate in CR included as research subjects.

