#### 2.3.2. Exclusion criteria.

-Patients contraindicated for cardiorespiratory exercise-stress testing and exercise training or those who had difficulty participating in this study because of other medical reasons and discretion by the researcher.-Contraindications included unstable angina symptoms, acute myocardial infarction (within 2 days), uncontrolled ventricular arrhythmias, 3rd-degree atrioventricular block without a pacemaker, acute congestive heart failure, severe aortic stenosis, acute systemic disease, thrombophlebitis or intracardiac thrombosis, active or suspected myocarditis, and pericarditis.-Patients determined to be at risk of serious health problems because of exercise training.

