### 2.6. Intervention method

#### 2.6.1. Experimental group.

The participants will participate in 36 outpatient rehabilitation exercise programs with incentives. Three CR sessions will be conducted weekly. The experimental group will receive 5000 (approx. 4 USD), 10,000 (7 USD), and 15,000 Korean Won (11 USD) per completed session of CR during the 1st to 12th, 13 to 24th, and 25th to 36th CR sessions, respectively. Participants who will complete the 36 sessions will receive ₩ 360,000 (260 USD) incentives.

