### 2.8. Data collection and analysis

#### 2.8.1. Assessment timing and assessment criteria.

All participants will complete baseline assessments and chart review (after consent), followed by assessments at 3 months after discharge (after the exercise program), and at 6 and 12 months after baseline evaluation (follow-up assessment) (Fig. 1).

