### 2.9. Outcome evaluation

#### 2.9.1. Primary outcome.

The primary outcomes at 3 months will be the CR participation rate, defined as the number of CR sessions completed, and the CR completion rate (attendance of sessions greater than 50%; thus, completion of ≥ 18 sessions). Changes in PROM functional status using the Korean activity scale index (KASI), quality of life assessments in EuroQol 5 dimensions, and depression evaluation using the patient health questionnaire will be compared from baseline to 3, 6, and 12 months.

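### Eligibility does not require randomisation before the first outpatient CR session or cap the time since discharge, and the 3-month assessment and the incentive run on different clocks

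*Protocol article*

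**What the plan says.** **Who is approached (section 2.3).** "Among the patients who visited the hospital for outpatient CR, the study objectives will be explained". The section goes on: "Separate recruitment notices will be posted in the therapy rooms of the rehabilitation center". The same sentence adds the outpatient clinics of Rehabilitation Medicine and Cardiology, and the next adds banners at the hospital entrance.

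**Who is eligible (sections 2.3.1 and 2.3.2).** Apart from age, the inclusion criteria are "Patients hospitalized for acute MI and referred for outpatient CR after acute treatment and discharge" and "Patients who agreed to participate in CR included as research subjects". The exclusions are contraindications, other medical reasons or researcher discretion, and exercise risk. The only time condition is the contraindication "acute myocardial infarction (within 2 days"), a lower bound that will rarely matter for a patient already discharged. Neither list mentions CR sessions already attended or a longest interval since the infarction or discharge.

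**What participants then do.** Both arms take part in 36 sessions, three a week over about 12 weeks (sections 2.6.1 to 2.6.3). The incentive is paid "per completed session of CR during the 1st to 12th, 13 to 24th, and 25th to 36th CR sessions" (section 2.6.1), and the Abstract says it runs for 3 months after enrollment.

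**When the outcome is taken.** The baseline assessment follows consent and is "followed by assessments at 3 months after discharge (after the exercise program") (section 2.8.1). The Abstract also dates the 3-month comparison from discharge. The number of sessions attended is collected at that visit. The completion outcome is "attendance of sessions greater than 50%; thus, completion of ≥ 18 sessions" (section 2.9.1).

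**The concern.** The described trial works only for patients who enter at session 1 and soon after discharge, and no eligibility rule secures either condition. Recruiting among people who come for outpatient CR, partly in the therapy rooms, makes it plausible that some have already begun.

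For a patient already under way, the protocol does not say whether earlier sessions count toward the 36, toward the 18, or toward the incentive tier. If they count, both arms carry sessions that the incentive could not have influenced. If they do not, the patient has still shown some willingness to attend, and the planned 15.4% control rate may not describe such patients.

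For a patient enrolled some time after discharge, the assessment date may fall before the program and the incentive period end. Sessions attended after that date would be missed, or the stated date would have to be ignored. The two hospitals could resolve this differently.

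Both primary outcomes are session counts or derived from them, so what is at stake is the meaning of the primary endpoint and the power to detect a difference in it.

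**Working it through.** **1. The plan's own figure.** Section 2.5 gives completion of 55.4% versus 15.4%, power 0.8 and 22 per group. Section 2.11 gives P < .05, taken here as two-sided. With pooled variance and no continuity correction, and mean rate p̄ = (0.554 + 0.154)/2 = 0.354:

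n = [1.96·√(2p̄(1−p̄)) + 0.842·√(p₁(1−p₁) + p₂(1−p₂))]² / (p₁−p₂)² = (1.3255 + 0.5170)² / 0.16 = 21.2, so 22.

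The stated 22 reproduces. Exact power of the uncorrected chi-square test at 22 per arm, by summing binomial probabilities over all outcome pairs, is 0.81.

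**2. The two clocks.**
- Program length: 36 sessions / 3 per week = 12 weeks.
- Assessment: 3 months after discharge, about 13 weeks.
- Slack: 13 − 12 = about 1 week. A patient whose first session comes later than that cannot finish all 36 by the assessment date, even with perfect attendance.
- Reaching 18 sessions takes 18 / 3 = 6 weeks. A patient starting more than 13 − 6 = about 7 weeks after discharge cannot reach 18 by that date in either arm.

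**3. Illustration of dilution.** Let a share f be established attenders who complete at 80% in both arms, with the rest following the plan. The rate in each arm is (1−f)·p + f·0.80. The share, the 80% and the absence of an incentive effect in these patients are all assumptions; the document gives none of them.

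| f | Incentive | Control | Difference | Exact power, 22 per arm |
|---|---|---|---|---|
| 0 | 55.4% | 15.4% | 40 points | 0.81 |
| 10% | 57.9% | 21.9% | 36 points | 0.69 |
| 20% | 60.3% | 28.3% | 32 points | 0.58 |
| 30% | 62.8% | 34.8% | 28 points | 0.46 |

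With 90% completion in place of 80%, power is 0.69, 0.58 and 0.46, so that assumption hardly matters. With all 24 per arm analysed, at 80%, power is 0.76, 0.65 and 0.53.

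**4. Relaxing the zero-effect assumption.** Take f = 20% and let the incentive also work in established attenders. The Introduction reports Korean participation falling from 47% to 17%; 17/47 = 36% serves as a lower completion rate for people who have started.
- 80% control, 95% incentive: power 0.66.
- 36% control, 56% incentive: power 0.70.
- 36% control, 76% incentive: power 0.79.

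The zero-effect assumption therefore drives much of the loss in step 3.

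**5. Late entrants.** If a share f cannot reach 18 sessions by the assessment date in either arm (completion 0%), the differences are again 36, 32 and 28 points. Power by the normal approximation is 0.74, 0.66 and 0.58 for f of 10%, 20% and 30%.

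**The case against.** The strongest reply is that the text already describes starters. Participants undertake 36 sessions, payment begins at the first, baseline exercise testing follows consent, and inclusion speaks of patients referred for CR who agree to take part. A 3-month visit after discharge that is also after a 12-week program implies prompt enrollment. Researchers may exclude at their discretion, a journal article condenses its protocol, and broad eligibility suits a pragmatic trial.

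Much of this stands as evidence of intent. It does not amount to a rule: a patient under way can meet every listed criterion. The full protocol may contain the missing line, but the clash between discharge and enrollment as starting points is in the published text itself. If the phrase placing the visit after the program is meant to govern, then dating it from discharge is wrong for anyone who starts late.

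A reader might infer more than the documents support:
- **That recruitment centres on the therapy rooms.** It does not: notices also go up in the clinics, where starters will see them.
- **That someone with 12 sessions behind them needs only 6 more to count as a completer.** Nothing says that sessions before randomisation count toward the 18, and Table 1 records participation in the 36-session program.
- **That established attenders will mostly complete whatever their arm.** The Introduction points the other way, with 26.9% completion among US participants and the Korean fall from 47% to 17%. Payments also rise with later sessions, so an effect on retention is plausible.

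**Conclusion.** The point holds as a gap between the eligibility rules and the design, together with a conflict over when the 3-month window starts. Followed as written, the criteria admit patients for whom the session count, the incentive tier and the primary assessment date are not well defined.

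The likely harm is dilution toward the null and a session count that means different things for different patients. A reader might infer bias between the arms; the documents do not support that, because randomisation protects against systematic imbalance in who has already started.

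A definite loss of power cannot be claimed either. The fall from 0.81 to between 0.69 and 0.46 requires 10% to 30% established attenders and no incentive effect in them. At 20%, power is 0.66 to 0.79 in the scenarios where the incentive does work in them. The timing conflict needs none of these assumptions: it follows from the 12-week program and the 3-month date, for anyone starting more than about a week after discharge.

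**What to change.** - In section 2.3.1, require that randomisation precede the first outpatient CR session for the index infarction. In section 2.3.2, exclude patients who have already attended one.
- Have the sponsor set a maximum interval from index discharge to randomisation.
- Count sessions, incentive tiers and the 3-month primary window from randomisation, and reconcile the Abstract and section 2.8.1 accordingly.

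The notices can stay where they are: once the eligibility lines are in place, their location does not matter.

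The cost is a few lines of protocol text and a slightly smaller screening pool, with perhaps slower accrual of the 48 patients. If recruitment has already begun, the same steps can be applied to later entrants, and sessions attended before randomisation should be recorded for those already in.

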#### 2.3.1. Selection criteria.

-Male and female patients aged between 19 and 85 years.-Patients hospitalized for acute MI and referred for outpatient CR after acute treatment and discharge.-Patients who agreed to participate in CR included as research subjects.

#### 2.3.2. Exclusion criteria.

-Patients contraindicated for cardiorespiratory exercise-stress testing and exercise training or those who had difficulty participating in this study because of other medical reasons and discretion by the researcher.-Contraindications included unstable angina symptoms, acute myocardial infarction (within 2 days), uncontrolled ventricular arrhythmias, 3rd-degree atrioventricular block without a pacemaker, acute congestive heart failure, severe aortic stenosis, acute systemic disease, thrombophlebitis or intracardiac thrombosis, active or suspected myocarditis, and pericarditis.-Patients determined to be at risk of serious health problems because of exercise training.

### 2.4. Binding and allocation

The control and experimental groups will be randomized, with each group having a 1:1 assignment ratio. Group assignments will be determined using computer-based random number generators and will be known only by the research assistant after opening a sealed envelope containing a computer-generated sequence sheet.

The participants will know which group they belong to; however, the assessor will not be aware of each participant’s group, and the participants will be instructed not to inform the assessor. The person managing the data will not know the subject group until the analysis of the study is complete. If any participant is included in the study discontinuation criteria, the principal investigator will reveal the blinding and progress to standard treatment.

### 2.5. Sample size

The sample size was based on the results of a study on providing incentives for CR (e.g., session-completion rate:55.4% vs 29.2%, *P* = .002).^[14]^ However, considering the low CR completion rate in Korea, the session-completion rate was revised to 55.4% versus 15.4% (*P* = .002), and the sample size power was 0.8, thereby requiring 22 subjects for each group. Additionally, considering a 10% dropout rate, 24 participants will be required for each group, resulting in 48 participants. Twenty-four participants (12 each in each group per hospital) will be recruited because this study will be conducted at 2 institutions.

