### 2.11. Statistical analysis

The analysis of this study was performed using an intention-to-treat and per-protocol method. CR participation, defined as the number of sessions completed, will be analyzed as a continuous variable using the student *t* test or Mann–Whitney *U* test, based on the normal distribution of the data. CR completion and categorical variables will be analyzed using chi-square or Fisher’s exact test. Missing data will be replaced using the last observation carried forward or the mean value. In the case of more than 20% of dropouts, missing data in the intent-to-treat analysis will be replaced using multiple imputations. The intention-to-treat population will include all enrolled participants, and the per-protocol analysis will include patients who have completed the 3-month evaluation.

Changes in secondary outcomes over time for the CPET, KASI, EuroQol 5 dimensions, and patient health questionnaire will be analyzed using paired t-tests with comparisons from baseline. Analyses will be conducted for each of the intervention, control, CR completion, and non-completed groups. For non-normal distributions, the Wilcoxon signed-rank test will be used.

Statistical significance will be set at *P* < .05, and SPSS version 20 (IBM SPSS Statistics, New York, NY) will be used for the statistical analysis.

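### The plan fixes 12 patients per arm in each hospital but leaves hospital out of both primary tests; stratifying costs almost nothing and can gain power

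*Protocol article*

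**What the plan says.** Section 2.5 of the protocol article assumes that "the session-completion rate was revised to 55.4% versus 15.4" percent, and states that "the sample size power was 0.8, thereby requiring 22 subjects for each group"; it then adds that "considering a 10% dropout rate, 24 participants will be required for each group, resulting in 48 participants". The same section divides the total by hospital: "Twenty-four participants (12 each in each group per hospital) will be recruited because this study will be conducted at 2 institutions".

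Section 2.4 describes 1:1 assignment by computer-generated random numbers, with the group "known only by the research assistant after opening a sealed envelope containing a computer-generated sequence sheet". It mentions neither hospital, nor strata, nor blocks.

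Section 2.11 names the primary tests. Session count is compared by t test or Mann-Whitney, "based on the normal distribution of the data". For the binary outcome, "CR completion and categorical variables will be analyzed using chi-square or" Fisher's exact test, with no rule for choosing. "Statistical significance will be set at *P* < .05"; sidedness is not given. No primary test contains hospital.

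**The concern.** A quota of 12 per arm in each hospital makes hospital a balanced factor by design. When a balanced factor also predicts the outcome, an analysis that ignores it leaves the between-hospital variation in the error term. The standard error is then too large, the test is conservative, and power is given away that the same 48 patients could supply.

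Whether hospital predicts attendance here is unknown. The Introduction names distance, transportation and cost as barriers for patients, which makes a hospital difference plausible, but nothing says that these two hospitals differ.

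At stake is the efficiency of a small trial. The open choice of test adds to this, because the two tests permitted for completion do not have the same power at the planned rates.

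**Working it through.** **1. The plan's own figure.** Inputs from 2.5 and 2.11: p1 = 0.554, p2 = 0.154, power 0.80, alpha 0.05 (two-sided assumed). The mean rate is 0.354.

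n = [1.960·√(2·0.354·0.646) + 0.842·√(0.554·0.446 + 0.154·0.846)]² / 0.400²
= [1.960·0.676 + 0.842·0.614]² / 0.16 = 21.2, so 22 per arm.

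The stated 22 reproduces as an uncorrected chi-square calculation with no hospital term.

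**2. Does the quota arise by itself?** Simple 1:1 randomisation of 24 patients in each hospital gives 12:12 in both with probability (C(24,12)/2²⁴)² = 0.161² = 2.6%. One shared 24:24 list gives it with probability C(24,12)²/C(48,24) = 22.7%. The quota therefore needs allocation controlled within hospital.

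**3. Completion, exact enumeration, 12 versus 12 in each hospital.** Let t and c be the completers per arm, with m = t + c; in hospital h, let a_h be the completers in the incentive arm and m_h all completers.
- Pooled chi-square: 48·[t(24 − c) − c(24 − t)]² / [24·24·m(48 − m)].
- Cochran-Mantel-Haenszel (CMH), uncorrected: [Σ(a_h − m_h/2)]² / Σ[12·12·m_h(24 − m_h)/(24²·23)].

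Both are compared with the 5% point of chi-square on 1 df. The hospital gap is an assumption, applied as plus and minus half the gap to both arms. At the planned rates it cannot exceed 2 × 15.4 = 30.8 points without a negative control rate, so the 40-point case uses a smaller effect.

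| Case | Chi-square power | CMH power |
|---|---|---|
| 55.4% vs 15.4%, no gap | 86.0% | 85.8% |
| same, 10-point gap | 86.1% | 86.1% |
| same, 20-point gap | 86.6% | 87.2% |
| same, 30-point gap | 87.4% | 89.8% |
| 30-point effect, 40-point gap (75% vs 45%; 35% vs 5%) | 60.0% | 65.9% |

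Under the null with a mean rate of 35%, type I error is:

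| Hospital gap | Chi-square | CMH |
|---|---|---|
| none | 5.2% | 5.2% |
| 20 points | 4.7% | 4.9% |
| 40 points (55% and 15%) | 3.2% | 4.8% |

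The slight excess over 5% with no gap comes from discreteness and is shared by both tests.

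**4. Session count, simulation (20,000 trials per case).** Assumptions: normal data, and a standardised effect of 0.83, which gives about 80% power at 24 per arm. An unadjusted t test is compared with a linear model containing group and hospital.

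| Hospital effect | Power, unadjusted | Power, adjusted | Type I error, unadjusted |
|---|---|---|---|
| 0 | 80.2% | 80.1% | 4.9% |
| 0.5 SD | 77.8% | 79.8% | 4.4% |
| 1 SD | 72.7% | 80.2% | 2.9% |
| 1.5 SD | 63.9% | 80.6% | 1.4% |

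The losses are about 2, 7.5 and 17 points. The adjusted model stands in for van Elteren here; the rank test itself was not simulated.

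**5. Choice of test.** Exact power at 55.4% versus 15.4%:
- 22 per arm: chi-square 81.5%, Fisher 72.3%.
- 24 per arm: chi-square 86.0%, Fisher 78.2%.
- Fisher only when an expected count is below 5: used in 1.5% of trials at 22 per arm and 0.5% at 24, with power 81.4% and 86.0%.

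For session count, choosing between t and Mann-Whitney after a normality test gave type I error of 4.8% to 5.5% in simulations under three assumed distributions, close to either test fixed in advance.

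**The case against.** Four objections carry weight.

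- **Validity.** A reader might infer that ignoring hospital, or choosing the test after looking at the data, makes the primary analysis invalid. Neither follows. A conservative test is valid, and the normality-based choice stays near 5%. Picking the smaller of the two p-values would raise the error to about 6% to 7%, but 2.11 does not say that this will be done.
- **Size of the gain.** Every power difference in favour of stratifying depends on a hospital effect that the documents do not give. For completion, the outcome used for sizing, the gain is slight unless the hospitals differ strongly. This stands and limits the point.
- **Fisher.** Chi-square or Fisher commonly means Fisher for small expected counts. Under that reading, power matches chi-square. The 72.3% figure needs Fisher in every case and 22 per arm, whereas the intention-to-treat set is all enrolled participants, so 24 per arm. What stands is that the rule is unstated and that routine Fisher falls short of 0.8 at either size.
- **Allocation text.** A reader might infer that 2.4 describes unrestricted randomisation and contradicts 2.5, or that an opened envelope reveals later assignments. Section 2.4 is silent on strata and blocks, and the quota itself implies allocation by hospital. An article may leave list and envelope details to the full protocol, and nothing shows that one sheet lists several patients' assignments. Neither inference is supported.

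**Conclusion.** The point holds as one of efficiency and consistency. The quota in 2.5 makes hospital a design factor, 2.4 does not state it, and the primary tests in 2.11 leave it out. The cost is conditional: nothing if the hospitals are alike, little on completion at the planned effect, and material on session count only at a hospital effect of about 1 SD or more. These figures rest on assumed hospital effects, two-sided testing, exactly 12 per cell and, for sessions, normal data. Because stratifying costs about 0.2 points at worst in the cases examined, the balance favours it. The sample size of 22 per arm before dropout is not in question.

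**What to change.** **Section 2.11, completion:** analyse by the Cochran-Mantel-Haenszel test stratified by hospital, without continuity correction, and report the hospital-stratified risk difference with its 95% confidence interval. This replaces the open choice between chi-square and Fisher for the primary outcome.

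**Section 2.11, session count:** name one hospital-stratified test in advance (van Elteren) and delete the choice based on normality.

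**Section 2.4:** state that allocation is made within hospital, so that it agrees with 2.5.

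The cost is a few sentences and a slightly longer analysis. No further patients or data are needed. The software should be checked to confirm that it gives the uncorrected CMH statistic and the stratified rank test.

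### The plan balances the arms within each hospital, but both primary tests ignore hospital; if attendance differs between the two sites, adjusting for hospital recovers power at almost no cost

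*Protocol article*

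**What the plan says.** Section 2.5 (Sample size) plans the arm sizes separately for the two hospitals: "Twenty-four participants (12 each in each group per hospital) will be recruited because this study will be conducted at 2 institutions". That is 24 per hospital and 48 in all.

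Section 2.4 (Binding and allocation) gives the ratio, "The control and experimental groups will be randomized, with each group having a 1:1 assignment ratio", and the source of the sequence, "Group assignments will be determined using computer-based random number generators". It names no strata.

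Section 2.11 (Statistical analysis) fixes the tests for the two primary outcomes. The session count "will be analyzed as a continuous variable using the student" t test, or the Mann–Whitney test if the data are not normal. For the other outcome, "CR completion and categorical variables will be analyzed using chi-square or" Fisher's exact test. No section of the article adds a hospital term or a stratified test for either primary outcome.

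**The concern.** Hospital is planned as a balancing factor and then dropped from the analysis. With 12 per arm at each hospital, the sites contribute equally to both arms, so a site difference in attendance cannot shift the estimated arm difference. An unstratified test still counts that difference as random variation, so its standard error is larger than the true sampling error of the contrast. Its type I error then falls below the nominal level and power is lost.

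A site difference is plausible. The Introduction names distance, transportation, time and cost as the main barriers to attendance, and these can vary between two hospitals' catchments. At stake is some power in a 48-patient trial, mainly for session count, for which the article gives no separate power calculation.

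**Working it through.** **Inputs from the article.** 12 per arm per hospital, 2 hospitals (2.5); completion 55.4% versus 15.4% ("the session-completion rate was revised to 55.4% versus 15.4", 2.5); power 0.8 (2.5); significance at 0.05 (2.11), taken as two-sided because sidedness is not stated.

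**Assumption.** The documents give no between-hospital difference in attendance, so a range is shown.

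**Step 1. Reproduce the planned size.** Two-sided, pooled variance, no continuity correction, mean rate (0.554 + 0.154)/2 = 0.354:

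n = [1.96 × √(2 × 0.354 × 0.646) + 0.8416 × √(0.554 × 0.446 + 0.154 × 0.846)]² / 0.40² = (1.3255 + 0.5170)² / 0.16 = 21.2, rounded up to 22 per group. This matches the plan ("the sample size power was 0.8, thereby requiring 22 subjects for each group"). The calculations below use the 24 per arm to be enrolled.

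**Step 2. What the unadjusted t test does to the variance.** Let the within-hospital SD be 1 and the hospital means differ by D. Each arm has 12 patients at +D/2 and 12 at −D/2, which adds 24 × D²/4 = 6D² to its sum of squares on 23 degrees of freedom. The expected variance estimate is 1 + 6D²/23. The true variance of the arm difference is unaffected by D, so the standard error is too large by a factor of about √(1 + 6D²/23).

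**Step 3. Session count.** Simulation with 100,000 trials per cell, normal data and an arm effect of 0.83 SD (about 80% power). The adjusted analysis is a linear model with arm and hospital on 45 residual degrees of freedom.

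| Hospital difference D (SD) | SE factor (step 2) | Type I error, t test | Power, t test | Power, with hospital | Loss (points) |
|---|---|---|---|---|---|
| 0 | 1.00 | 0.049 | 80.2% | 80.2% | 0.0 |
| 0.25 | 1.01 | 0.048 | 79.8% | 80.3% | 0.4 |
| 0.5 | 1.03 | 0.044 | 78.7% | 80.5% | 1.8 |
| 0.8 | 1.08 | 0.034 | 75.7% | 80.3% | 4.7 |
| 1.0 | 1.12 | 0.028 | 72.8% | 80.3% | 7.4 |
| 1.5 | 1.26 | 0.014 | 63.1% | 80.2% | 17.0 |

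Type I error of the adjusted model stays at 0.049 to 0.051 throughout.

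**Step 4. Completion.** Exact enumeration at the planned rates, 12 per arm per hospital, with the same absolute hospital gap in both arms (rates set at the planned rate plus and minus half the gap).

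| Hospital gap (percentage points) | Power, chi-square | Power, Cochran–Mantel–Haenszel | Loss (points) |
|---|---|---|---|
| 0 | 86.0% | 85.8% | −0.2 |
| 10 | 86.1% | 86.1% | 0.0 |
| 20 | 86.6% | 87.2% | 0.6 |
| 30 | 87.4% | 89.8% | 2.4 |

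A 30-point gap is close to the ceiling. With equal hospitals and a 15.4% average in the control arm, the widest possible split is 0% and 2 × 15.4% = 30.8%.

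Under no arm effect, at a common 35.4% rate, the type I error of chi-square is 0.045, 0.037 and 0.026 for hospital odds ratios of 3, 5 and 10. For Cochran–Mantel–Haenszel it is 0.048 to 0.049.

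**Step 5. Does the stated allocation deliver the balance?** Unrestricted 1:1 allocation of 24 patients gives 12:12 with probability C(24,12)/2²⁴ = 0.161, and at both hospitals with probability 0.161² = 0.026. Exact balance therefore needs a sequence restricted within hospital, which 2.4 does not mention.

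**The case against.** - **No hospital difference is shown.** This stands. Both sites are tertiary hospitals delivering the same 36-session programme, and with no difference there is nothing to recover. Every figure above is conditional on an assumed gap.
- **The t test may not be the test used.** This also stands. Session counts are likely to be skewed, and 2.11 then moves to Mann–Whitney. In simulations with strongly non-normal counts and an assumed 9-session effect, Mann–Whitney fell short of its hospital-stratified version (van Elteren) by about 1.5 points at a 4-session hospital gap, about 5 at 8 sessions and about 10 at 12 sessions. The direction is the same, and the loss matters only for large gaps.
- **The per-hospital figure may be only a recruitment target.** This is possible. Balance would then be approximate and the unadjusted tests less conservative, but adjustment would still be sound.
- **The analysis plan may adjust for hospital.** It is not shown and may do so. The article does, however, name the primary tests, and those tests do not use hospital.

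A reader might infer more: that the primary P values are certainly too large, that the completion test is underpowered because hospital is ignored, or that the tests are biased or invalid. The documents support none of these. The first needs a hospital difference they do not report. On the second, chi-square stays at 86–87% power at the planned rates; much larger losses appear only under a weaker assumed effect or control rates that do not fit the plan. A split of 9% and 44%, for example, averages 26.5%, not 15.4%. On the third, the unadjusted contrast is unbiased under balance, and ignoring hospital lowers the type I error.

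**Conclusion.** The point holds as a conditional efficiency gain. The plan balances on hospital and then leaves it out of both primary tests. If the hospitals differ in attendance, those tests remain valid but are conservative.

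The gain is mainly for session count: negligible for small site differences and material from about 0.8 SD upwards. For completion it is small across the gaps that the planned rates allow.

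This rests on an assumed hospital difference, exact 12:12 balance within hospital, two-sided 5% tests and, for the session-count table, normal data with an effect sized for about 80% power.

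**What to change.** In 2.11, make the hospital-adjusted analyses primary, and fix this before the arms are unmasked:

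- **Session count:** a linear model with arm and hospital, reporting the adjusted mean difference with its 95% confidence interval; a van Elteren test if the rank-test branch applies.
- **Completion:** a Cochran–Mantel–Haenszel test, with a hospital-stratified risk difference and its 95% confidence interval.
- **Unstratified tests:** keep them as supportive analyses.

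As a clarification only, 2.4 should say whether the sequence is restricted within hospital or the 12 per arm is a recruitment target.

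The cost is a change of wording and one degree of freedom, spent on a factor known for every patient. No extra patients or data are needed, and with no hospital difference the power is practically unchanged (80.2% either way for session count; 86.0% versus 85.8% for completion).
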